##### Responder analysis

CGH days, pain, and disability, as well as neck pain will be dichotomized using a 50% improvement threshold to define a responder. This is a common measure of important improvement in headache research [38]. The dichotomized data will be analyzed using binomial regression models [60] with the same independent variables as the primary analysis to compare responder rates between groups.

#### Secondary aim: economic analysis

Incremental cost-effectiveness ratios (ICERs) will be computed using adjusted between-groups differences in costs (numerator) and effects (denominator). Incremental cost-utility ratios will be computed replacing the denominator with quality-adjusted life years (QALYs) derived from the EuroQol EQ-5D [41, 42]. Regression analyses will be used to model cost and effect separately to adjust each for potential confounding variables [64–66], with bias-corrected and accelerated non-parametric bootstrap used to address cost-data skewness [67]. Bootstrapped cost-effect pairs will be plotted on the cost-effectiveness plane to assess the amount of uncertainty surrounding ICER estimates. In addition, cost-effectiveness acceptability curves will be used to estimate the probability of cost-effectiveness over a range of willingness to pay thresholds [68].

The principal cost analysis will consider only the scheduled treatment visits defined in this protocol. A second approach will adopt a societal perspective including all healthcare resources [51, 69, 70] and estimated costs of lost productivity due to CGH [71, 72].

#### Tertiary aim: effects of expectation

##### Quantitative analysis

The potential effects of patient expectancy will be explored in a path analysis using structural equation modeling [73, 74] as in our earlier work [26, 75]. Dose effects will be included in a measurement model, and expectancy variables will be permitted to affect subsequent outcomes, as well as being influenced by previous outcomes. Due to the limited sample size, this analysis will be carried out as an exploratory analysis.

##### Qualitative analysis

For the qualitative interviews, content analysis using an inductive approach [76] will be used to identify categories and themes that occur in the transcribed text [77]. Transcribed data will be entered into a database designed to capture and analyze qualitative data. The frequency of themes will be quantified and representative quotations will be identified [77, 78]. The frequency of responses in the thematic categories will be cross-tabulated with treatment group assignment and compared for between group differences using Chi-square analysis. 95% confidence intervals will be calculated for these differences.

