#### Treatment dose

Participants are randomized to one of four doses (*n* = 64 per group): 0, 6, 12, or 18 SMT visits. All participants are assigned 18 total visits. When participants do not receive the index therapy (SMT), they receive the control therapy (light massage).

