### Power analysis and sample size

A power analysis was conducted by simulating the primary analysis outlined above using the primary outcome, CGH days. We will randomize 256 participants (*n* = 64/group). Sample size is based on 80% power using a two-sided test at the .05 level of significance. For the primary outcome, CGH days, we will be able to detect a linear dose effect (slope) of 1.1 CGH days (between two adjacent doses) and a mean difference of 3.5 CGH days between 2 groups. The residual standard deviation of 7 headaches (surrogate for days) was used, based on regression analyses in the CGH pilot study [29]. The study will also be appropriately powered for CGH intensity, the principal secondary outcome.

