## Discussion

This novel study is the first full-scale randomized controlled trial aimed at identifying the dose of SMT to treat cervicogenic headache in an adult population. The long-term goal is to begin to set the clinical study standards to establish criteria that can be used to inform the decision-making process to 1) select optimal chiropractic care protocols for future comparative effectiveness trials and 2) determine the appropriate number, frequency, and duration of various chiropractic services for headache and other commonly treated neuromusculoskeletal conditions. Further, the use of a daily electronic headache diary to capture principal headache outcomes in real-time in both the short and long-term provides data arguably less subject to recall bias compared to other platforms such as paper diaries. To our knowledge, electronic diaries have not been used to collect headache outcomes in other CGH studies.

Headache is the most common pain condition resulting in lost work productivity, but cost data specific to CGH is lacking in the US [71]. Secondary outcomes used in this study will provide important information about the cost-effectiveness of SMT for CGH in adults. Further, several studies suggest a link between patient expectations and health outcomes [79–81]. However, in a pilot RCT, patient perception of the patient-provider interaction and patient expectations were balanced across groups and demonstrated little effect on outcomes [26]. To our knowledge, this is the first trial to use a qualitative and quantitative analysis to investigate the relationship of SMT dose to possible correlates including patient expectations, the patient-provider encounter, and headache outcomes. Information gathered will help to inform the design of future research and treatment regimens for patients with costly and prevalent headache conditions.

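### The interview-theme comparison does not use the order of the four SMT doses; a trend test should be added beside the chi-square, gaining up to about 17 points of power if a theme changes roughly linearly with dose

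*Protocol article*

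**What the plan says.** The Qualitative analysis section of the protocol article says that the frequency of responses in the thematic categories will be "cross-tabulated with treatment group assignment and compared for between group differences using Chi-square analysis", and that "95% confidence intervals will be calculated for these differences". It names no trend version of the chi-square and no dose scores.

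Under Treatment dose, the groups being compared are "0, 6, 12, or 18 SMT visits", with 64 participants planned in each. The Discussion describes the combined qualitative and quantitative analysis as a way to "investigate the relationship of SMT dose to possible correlates including patient expectations".

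The Primary analysis section enters dose in two ways: as a linear or nonlinear function, and as indicators comparing each SMT group with control. The Responder analysis section reuses those independent variables for binary outcomes. The article does not say how many participants are interviewed, what theme frequencies are expected, or what power this comparison has.

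**The concern.** A Pearson chi-square on four groups gives the same result if the group labels are shuffled, so it cannot use the fact that the groups are 0, 6, 12 and 18 visits. The primary and responder analyses take both an ordered and an unordered view of dose. The theme comparison keeps only the unordered one, although relating dose to expectations is a stated purpose of this part of the trial.

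Two things follow. A theme that becomes steadily more or less common with dose may be missed more often than the design requires. And a significant 3-df result, taken alone, says only that the groups differ somewhere. The planned confidence intervals would show direction between groups but give no single estimate of change per dose step.

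**Working it through.** **Inputs from the article.** Four equally spaced doses (Treatment dose). "We will randomize 256 participants", that is 256/4 = 64 per group, and a two-sided 5% level (Power analysis and sample size).

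**Assumptions.** The number interviewed per arm, *n*, and the theme rates are not stated. I take *n* = 64 (everyone interviewed) and then *n* = 20, with each participant counted once per theme. The 5% level, stated for the primary outcome, is used here too.

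**The plan's own power figure.** There is none for themes. The one given is for headache days: "Sample size is based on 80% power using a two-sided test at the .05 level of significance". With SD 7, the article expects that a trial of this size will "detect a linear dose effect (slope) of 1.1 CGH days (between two adjacent doses) and a mean difference of 3.5 CGH days between 2 groups".
- Slope: with scores −1.5, −0.5, 0.5, 1.5 the sum of squares is 5, so SE = 7/√(64 × 5) = 0.391. Then 1.1/0.391 = 2.81 and power = Φ(2.81 − 1.96) = 0.80.
- Two groups: SE = 7 × √(2/64) = 1.237. Then 3.5/1.237 = 2.83 and power is 0.81.

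Both reproduce. The sample size was thus stated for an ordered slope as well as for pairwise differences.

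**Power for a theme.** Let p̄ be the mean rate over the four arms, dᵢ = pᵢ − p̄, and sᵢ the scores above. The noncentralities are:
- 3-df Pearson: λ₃ = n Σdᵢ² / [p̄(1 − p̄)], critical value 7.815
- 1-df Cochran-Armitage trend: λ₁ = n (Σsᵢdᵢ)² / [5 p̄(1 − p̄)], critical value 3.841

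Worked case, 30% rising evenly to 50%, n = 64: p̄ = 0.40 and Σdᵢ² = 0.0222, so λ₃ = 64 × 0.0222/0.24 = 5.93. The gradient is exactly linear, so λ₁ = λ₃. Noncentral chi-square power is 51.3% (3 df) against 68.2% (1 df), a gap of 17 points. Simulation of 40,000 tables gave 51.3% and 68.5%.

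| Rates at 0, 6, 12, 18 visits (n = 64) | λ₃ | λ₁ | 3-df | Trend | Trend minus 3-df |
|---|---|---|---|---|---|
| 30-37-43-50% | 5.93 | 5.93 | 51% | 68% | +17 |
| 20-27-33-40% | 6.77 | 6.77 | 57% | 74% | +17 |
| 20-25-30-35% | 4.01 | 4.01 | 36% | 52% | +16 |
| 20-30-40-50% (steep) | 14.07 | 14.07 | 90% | 96% | about +7 |
| 20-30-40-40% (levels off) | 8.02 | 7.15 | 66% | 76% | +11 |
| 20-35-40-40% | 7.69 | 6.05 | 64% | 69% | +6 |
| 20-40-40-40% (plateau) | 8.44 | 5.06 | 68% | 61% | −7 |
| 20-20-20-40% (threshold) | 10.24 | 6.14 | 77% | 70% | −7 |
| 20-40-40-20% (rise and fall) | 12.19 | 0 | 85% | 5% | −80 |

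**Ceiling.** Setting λ₁ = λ₃ = λ and varying λ, the gap peaks at 17 points for λ between 5 and 6. It is at least 15 points only for λ of about 3.7 to 8.2, where the trend test has roughly 48% to 82% power. At 80% trend power the 3-df test has 64.5%.

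**Fewer interviewed, n = 20.** The gap is 7 points for 20-25-30-35% (13% against 20%), about 10 for 30% to 50% (18% against 28%), and 16 for 20-30-40-50% (39% against 55%). For the plateau the two tests are equal, at 24%.

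**The case against.** The themes are found inductively and carry no stated direction. The hypothesis that more visits do better concerns headache frequency only, and some interview topics, such as lived experience with headaches, need not vary with dose. An omnibus comparison is a reasonable default there, and unordered group comparison is already half of the primary analysis. The cross-tabulation and its confidence intervals would also let a reader see the direction across doses. All of this stands. It is why the chi-square should stay and why the point is minor.

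It can also be said that chi-square analysis does not exclude a chi-square for trend, and that the version is a detail for the analysis plan. Strictly so, but the article does name a comparison, and its reference to between-group differences points to the unordered test. If a trend test was meant, a few words would settle it.

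Two stronger readings are tempting and are not supported:
- **That the plan loses 15 to 17 points for any dose-related theme.** That size needs a linear gradient of moderate strength. Plateau, threshold and rise-and-fall patterns are dose-related too, and there the omnibus test wins. The primary analysis itself allows for nonlinear dose effects.
- **That the tertiary aim never connects expectations to outcomes, because themes are tabulated only against group.** The Quantitative analysis section covers that link: its path analysis includes dose effects and lets expectancy variables affect later outcomes. The aim is mixed-methods, so the theme comparison need not do this as well.

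**Conclusion.** The point holds as a minor one. Read naturally, the theme comparison leaves dose order unused although the Discussion states a dose question. The loss is at most about 17 points of power, and only for a roughly linear theme gradient of moderate strength. The 51% against 68% example rests on assumed theme rates and on all 64 per arm being interviewed, neither of which the article gives. For plateau or non-monotone patterns the planned test is equal or better, so it should not be replaced. This is a tertiary comparison of exploratory themes; the primary and secondary conclusions do not depend on it.

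**What to change.** Keep the omnibus chi-square and the confidence intervals for group differences. Add, for each theme, a prespecified 1-df trend test on assigned dose with scores 0, 6, 12 and 18 (Cochran-Armitage, or binomial regression on dose in line with the responder analysis), and report the change per dose step with its 95% confidence interval.

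Check departure from trend with the 2-df remainder, that is the 3-df statistic minus the trend statistic. The full 3-df chi-square does not serve for this: in the exactly linear 30% to 50% case it rejects 51% of the time although there is no departure.

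The cost is a sentence or two in the analysis plan and one extra exploratory test per theme, on data already collected. The trend test has little or no power for non-monotone patterns, which the retained omnibus test covers. The wording should be settled before themes are compared by group.

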### Power analysis and sample size

A power analysis was conducted by simulating the primary analysis outlined above using the primary outcome, CGH days. We will randomize 256 participants (*n* = 64/group). Sample size is based on 80% power using a two-sided test at the .05 level of significance. For the primary outcome, CGH days, we will be able to detect a linear dose effect (slope) of 1.1 CGH days (between two adjacent doses) and a mean difference of 3.5 CGH days between 2 groups. The residual standard deviation of 7 headaches (surrogate for days) was used, based on regression analyses in the CGH pilot study [29]. The study will also be appropriately powered for CGH intensity, the principal secondary outcome.

### Data and safety monitoring plan

University of Western States is the data coordinating center responsible for the creation of case-report forms, data transfer and management. The data and safety monitoring board and 2 university institutional review boards meet annually to review the study. Reportable adverse events will be reviewed as they occur. No interim analyses are planned due to the low risk profiles of the interventions used in this study.

### Study status

Enrollment is complete at the Minnesota and Oregon sites. Follow-up data collection is ongoing thru 2016.

## Discussion

This novel study is the first full-scale randomized controlled trial aimed at identifying the dose of SMT to treat cervicogenic headache in an adult population. The long-term goal is to begin to set the clinical study standards to establish criteria that can be used to inform the decision-making process to 1) select optimal chiropractic care protocols for future comparative effectiveness trials and 2) determine the appropriate number, frequency, and duration of various chiropractic services for headache and other commonly treated neuromusculoskeletal conditions. Further, the use of a daily electronic headache diary to capture principal headache outcomes in real-time in both the short and long-term provides data arguably less subject to recall bias compared to other platforms such as paper diaries. To our knowledge, electronic diaries have not been used to collect headache outcomes in other CGH studies.

Headache is the most common pain condition resulting in lost work productivity, but cost data specific to CGH is lacking in the US [71]. Secondary outcomes used in this study will provide important information about the cost-effectiveness of SMT for CGH in adults. Further, several studies suggest a link between patient expectations and health outcomes [79–81]. However, in a pilot RCT, patient perception of the patient-provider interaction and patient expectations were balanced across groups and demonstrated little effect on outcomes [26]. To our knowledge, this is the first trial to use a qualitative and quantitative analysis to investigate the relationship of SMT dose to possible correlates including patient expectations, the patient-provider encounter, and headache outcomes. Information gathered will help to inform the design of future research and treatment regimens for patients with costly and prevalent headache conditions.

Notably, the fastidious nature of this trial and its methodologically rigorous design enhances internal validity. Specifically, the treatments are compared under tightly controlled conditions. Attention bias is controlled by standardized 10-min visits, equal number of visits, and restriction on concomitant care unassociated with the study. Patient expectation is controlled, in the absence of blinding, by equal enthusiasm for care by each chiropractor across treatment groups. The design also isolates the effects of manipulation by controlling the hands on time and attention from the chiropractor. In addition, strict eligibility criteria minimize the heterogeneity of the study population. To determine eligibility and ensure participant compliance, 2 baseline visits with a 4-week headache diary in between is strictly adhered to. Also, electronic diaries capturing headache outcomes are closely monitored and patients are reminded regularly to complete their diaries daily. To enhance generalizability, multiple recruitment strategies are used and participants are enrolled at 2 sites (West Coast and Midwest, USA).

Following completion of this trial, the study will provide dosing information and methodologically sound clinical evidence to inform the design of future comparative effectiveness trials and establish treatment protocols for patients suffering with CGH, a widespread and costly condition.

## Abbreviations

CGH, cervicogenic headache; CONSORT, Consolidated Standards of Reporting Trials; ICHD, International Classification of Headache Disorders; IHS, International Headache Society; IRB, institutional review board; LM, light massage; MN, Minnesota; OR, Oregon; RCT, randomized controlled trial; SMS, short message service; SMT, spinal manipulation therapy
